### Allocation and blinding

The randomization and sequence allocation will be performed according to a computer-generated randomization list by building a stratified randomization with permutated block-randomization, stratified by maternal body mass index (BMI) (<25, 25–29.9, and ≥30 kg/m^2^), and parity (1 or >1), in an allocation ratio of 1:1 in blocks of 4–6. The Group #1 will receive standard obstetrical and gynecological follow-up and nutritional counseling to promote MD provided by certified dietitians, and the Group #2: will receive standard obstetrical and gynecological follow-up alone. Due to the nature of the RCT design, participants and RT will be aware of the group assignment. Whereas the allocation to Group #1 or Group #2 will remain unknown to the CT and ST.

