### Study design

The PREMEDI Study will be a 9-month multi-center, randomized-controlled, parallel groups, prospective trial.

The study will involve three parallel teams: Research Team (RT), Clinical Team (CT), and Statistical Team (ST). The RT will be composed by physicians, molecular biologists, and dietitians. The CT will be composed by gynecologists, neonatologists, pediatricians, family pediatricians, allergologists, dietitians, and pediatric nurses. The ST will be composed by statisticians. A Study Monitor will overview the trial’s data management and analysis.

The RT will be dedicated to the enrollment and the randomization of participants. Then, the dietitians of the RT will perform the personalized nutritional counseling during the study phases. The CT will evaluate the participants and will collect data in anonymous form and will deliver data to the ST. The ST, unaware of study cohorts, will review the study dataset and will undergo data cleaning and verification according to standard procedures. Finally, ST will lock the database once it will be declared complete and accurate and will perform statistical analysis.

The graphical representation of study design is reported in Figure 1.

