### Metagenomic and metabolomic analysis

All fecal and human milk samples will be stored at −80°C and subjected to microbial DNA extraction by RT according to the International Human Microbiome Standard Consortium (IHMSC) Standard Operating Procedures (23).

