### Epigenetic analyses

Emerging data support the concept that epigenetic mechanisms could drive the occurrence of allergic diseases. Epigenetic biomarkers have been pointed out, suggesting the role of selected methylation rate of the promoter region of Th1 and Th2 cytokine genes and of selected microRNAs expression. We will investigate these biomarkers with targeted DNA methylation analysis with the aim to link the MD adherence with the expression of these biomarkers and clinical outcome also through mediation analysis. Parallelly, we will attempt at epigenome-wide evaluation to explore the potential role of other epigenetic mechanism elicited by MD during pregnancy as protective action against allergy.

Cord blood will be collected by CT team in two EDTA-tubes (5 ml/each) and immediately transported to the laboratory for DNA and RNA extraction using the Extraction Kit (GE Healthcare, Chicago, IL, USA) performed by RT. One microgram of extracted DNA will be modified with sodium bisulfite to convert all unmethylated, but not methylated-cytosine to uracil. Bisulfite conversion will be carried out using the EZ DNA Methylation Gold Kit (ZYMO Research Co., Orange, CA, USA), according to the manufacturer’s instructions. The converted DNA will be stored at −80°C until used.

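### Nucleic-acid extraction from stool, milk and cord blood is assigned to the Research Team, which is declared aware of allocation, although nothing in the intervention requires laboratory staff to be unmasked

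*Protocol article*

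**What the plan says.** All statements are in the protocol article.

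- **Who knows the allocation** (Allocation and blinding): "Due to the nature of the RCT design, participants and RT will be aware of the group assignment".
- **Who is masked** (same section): "Whereas the allocation to Group #1 or Group #2 will remain unknown to the CT and ST". CT is the Clinical Team and ST the Statistical Team. No other group is named as masked.
- **Who is in the RT** (Study design): "The RT will be composed by physicians, molecular biologists, and dietitians". Molecular biologists are listed in neither of the other two teams. The same section gives the RT a further role: "The RT will be dedicated to the enrollment and the randomization of participants". Its dietitians also counsel Group 1.
- **Stool and milk** (Metagenomic and metabolomic analysis): the samples are "subjected to microbial DNA extraction by RT according to the International Human Microbiome Standard Consortium (IHMSC) Standard Operating Procedures".
- **Cord blood** (Epigenetic analyses): "Cord blood will be collected by CT team in two EDTA-tubes", and the tubes are then "immediately transported to the laboratory for DNA and RNA extraction using the Extraction Kit (GE Healthcare, Chicago, IL, USA) performed by RT".
- **What depends on these samples** (Study outcomes): metagenomic and metabolomic features of mother and child, breast milk composition, and epigenetic modulation in the offspring. All are secondary outcomes.

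The anonymity described under Study design and Data entry concerns the collected data and the database. It is not stated for specimens in the laboratory.

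**The concern.** The masking rule is drawn by team, and the laboratory falls on the unmasked side. The reason given is the nature of the design. That explains why a counseled woman and her dietitian must know the group; it does not explain why a person extracting DNA from a tube should know it. The article takes a position here and the position is weaker than it needs to be, so this is more than a detail left out.

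Sequencing, methylation and expression measurements are sensitive to technical conditions such as extraction run, plate and repeat handling. Staff who know the group could, without intending it, let order, repeats or rejection of samples differ between groups. A difference that enters at this stage comes before the data reach the masked ST, whose masking cannot remove it. The analyses under Statistical methods (Wilcoxon comparisons of taxa and genes, a random-forest classifier, methylation models) would read it as an effect of the diet. In the extreme case where run and group coincide, the two effects cannot be separated afterwards.

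**Working it through.** **Step 1. Trace each laboratory step to a team.**

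| Step | Team named | Masked? |
|---|---|---|
| Stool sampling at pregnancy visits (infant stool is also among the CT visit procedures) | CT | yes |
| Cord-blood collection | CT | yes |
| Microbial DNA extraction, stool and milk | RT | no |
| DNA and RNA extraction, cord blood | RT | no |
| Shotgun sequencing | none named | not stated |
| Short-chain fatty acids by GC-MS | none named | not stated |
| Bisulfite amplicon sequencing | none named | not stated |
| Methylation array, miRNA cards | none named | not stated |
| Statistical analysis | ST | yes |

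The two extraction steps are therefore expressly given to a team declared unmasked. They feed the metagenomic, methylation and miRNA outcomes. The short-chain fatty acid measurement involves no nucleic-acid extraction, and no team is named for it.

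**Step 2. The only sample-size figure in the plan.** The plan has no figure for laboratory bias. Its 138 pairs per group is needed only as an input. It is close to the two-proportion formula with unpooled variance: [0.30×0.70 + 0.15×0.85] × (1.960 + 0.842)² / 0.15² = 0.3375 × 7.849 / 0.0225 = 117.7, so 118, and 118/0.85 = 138.8, so 139 against the stated 138. The number remaining after 15% drop-out is 138 × 0.85 = 117.3, taken as 117.

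**Step 3. Illustrative upper bound.** Assumptions, none from the documents: 117 usable samples per group, a technical shift of d SD, and complete coincidence of batch and group. For one comparison, z = d / √(2/117) = d / 0.1307. The two-sided rejection probability with no true effect is 1 − Φ(c − z) + Φ(−c − z), with c = 1.960 at the 5% level.

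| Assumed shift d | z | Rejection at 5% | Rejection at 0.05/377 |
|---|---|---|---|
| 0.1 SD | 0.76 | 12% | 0.1% |
| 0.2 SD | 1.53 | 33% | 1.1% |
| 0.3 SD | 2.29 | 63% | 6.3% |
| 0.5 SD | 3.82 | 97% | 50% |

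The last column treats the 377 miRNAs as one Bonferroni family (my assumption), so c = 3.82 and the nominal rate is 0.05/377 = 0.013%.

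**Step 4. How fast this falls with partial alignment.** Suppose there are two batches and one holds 60% of one group and 40% of the other. The shift between groups is then (0.60 − 0.40) × d. For d = 0.3 SD this is 0.06 SD, z = 0.06/0.1307 = 0.46, and the rejection rate is about 7.4% instead of 63%.

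**The case against.** **Only extraction is assigned to the RT.** A reader might infer from the molecular biologists' place in the RT that this team produces every laboratory outcome. The text does not say so. No team is named for sequencing, GC-MS, arrays or miRNA cards, and the figure that names the executing team is not shown. This objection stands, and the point is limited to extraction.

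**Nobody is said to batch by group.** A reader might also infer that unmasked staff decide run order, repeats and rejection of samples. The article is silent on all of these. Cord blood goes to the laboratory at once, so its extraction order will tend to follow delivery dates, and 1:1 allocation in blocks of 4–6 limits drift between group and calendar time within strata. Extraction from stool and milk follows standard operating procedures. This also stands: full alignment is an extreme and is not prescribed by the protocol.

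**The error rates are uncorrected.** Statistical methods foresees Bonferroni adjustment, and false discovery rate control for pangene prevalence. The 33% to 97% figures are therefore not the planned per-feature rates. That is right. Correction lowers the rate per feature but does not remove the bias: at 0.3 SD, 6.3% is still far above 0.013%.

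**Laboratory detail belongs elsewhere.** Tube codes and plate layout may sit in a full protocol or laboratory manual, and their absence from an article would be no finding. This is fair for those details. It does not cover the masking statement, which the article makes itself and which leaves the whole RT unmasked.

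**Conclusion.** The point holds in a limited form. The protocol assigns nucleic-acid extraction from stool, milk and cord blood to a team it declares aware of allocation, and the reason it gives does not apply to laboratory staff. This opens an avoidable route to bias in the secondary metagenomic, methylation and miRNA outcomes.

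The primary outcome is not touched, because the masked CT assesses it, and the masked ST carries out the statistical analysis. The documents do not show that bias will occur. They give no batch-effect size, do not tie batches to group, and do not say who runs the later assays. The calculated rates are an upper bound under full alignment and chosen shifts, before multiplicity correction; they are not an estimate for this trial.

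The case for acting rests on the low cost of closing the route. It should be changed, but it does not threaten the main result.

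**What to change.** In Allocation and blinding, limit the unmasked members of the RT to those who enroll, randomize and counsel, and state that laboratory staff are masked.

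To make this work:

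1. The masked CT, which already takes stool and cord blood, labels each sample (milk included) with a code that does not reveal the group.
2. The key is held outside the laboratory, for example by the Study Monitor, until the laboratory data are locked.
3. Extraction and assay runs are filled in random order or balanced by group.
4. The run number is recorded, so that any remaining imbalance can be examined.

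If the laboratory already works on coded samples, one sentence saying so is enough for the masking part.

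The cost is sample labels, a run list and slightly more logistics. No extra staff, visits or assays are needed.

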### Study outcomes

The main study outcome will be the evaluation of the effect of MD during pregnancy on the occurrence of allergic disorders at 24 months of age in the offspring.

Secondary study outcomes will include the evaluation of:

–women MD-adherence score (Med Diet Score);–maternal weight gain and pregnancy complications (including gestational diabetes, arterial hypertension, gestosis, cholestasis, premature rupture of membranes (PROM), placental abruption, post-partum anemia, post-partum hemorrhage);–perinatal complications (including intrauterine growth retardation (IUGR), small-for-gestational-age infant (SGA), large-for-gestational-age infant (LGA), preterm delivery, and fetal malformation) and neonatal birth weight;–body growth indices and occurrence of infectious diseases and chronic non-transmissible conditions (obesity, autoimmune diseases, malignancies, neuropsychiatric disorders) in the first 2 years of age in the offspring;–mother-child pair GM metagenomic and metabolomic features;–exclusive and overall breastfeeding duration and breast milk composition;–epigenetic modulation of genes involved in the regulation of immune system and metabolic pathways in the offspring;–child MD-quality Index score (KIDMED).

### Interventions

All enrolled women will receive, by the CT gynecologists, recommendations about the importance of an adequate energy intake, optimal weight gain during pregnancy based on pre-pregnancy Body Mass Index (BMI) (17) and hygiene rules for the prevention of major foodborne illnesses during pregnancy according to the guidance provided by the Italian Ministry of Health (18). They were also recommended to walk ≥30 min/day. All enrolled women will be instructed on how to complete the 7-day food diary by the RT dietitians.

Only for women enrolled in the Group #1, a nutritional counseling will be provided by the RT dietitians. The RT dietitians will deliver the nutritional counseling over three face-to-face sessions, which will include a session at enrollment (8–13 GW), and two further sessions after 3 months from enrollment (14–28 GW) and after 6 months from enrollment (29–40 GW). The nutritional counseling will be based on a Mediterranean-style Diet. The key components of this diet will include the use of extra virgin olive oil as main cooking fat (at least four tablespoons/day), high intake of vegetables (two servings/day), fruits (three servings/day) (avoiding juices) and wholegrain cereals (three servings/day), three servings of skimmed dairy products/day, 2–3 servings of legumes/week, three servings of fish/week, three servings of nuts and seeds/week, drink at least two liters of water daily, a low consumption of red meat and processed meat, avoidance of refined grains, processed baked goods, pre-sliced bread, soft drinks and fresh juices, fast foods, and precooked meals.

Furthermore, after delivery, the CT will encourage women of both groups to breastfed wherever possible, to not avoid dietary food allergens during breastfeeding, to avoid the use of regular cow’s milk formula as supplementary feed for breastfed infants in the first week of life, and to introduce complementary feeding from 4 to 6 months of age, according to the European Academy of Allergy and Clinical Immunology guidelines for allergy prevention (19).

The decision to interrupt the study participation may take place at any time even without providing any explanation or justification, it will not entail any penalty, loss of benefits or loss of legal rights for mother-child pair and the mother-child personal data will always remain confidential.

### Data and sample collection

At baseline, after the first evaluation by the RT and the collection of written informed consent form, the CT will collect the following variables in a dedicated chart: anamnestic and clinical features, personal and anthropometric data, socio-demographic factors, gestational age, allergies, number of cohabitants, pets, sports activities, use of drugs, smoking exposure, education level, family and living conditions. At enrollment a validated questionnaire on MD-adherence (Med Diet Score) and a 7-day food diary (five weekdays and two weekend days) will be collected. The 7-day food dairy data will be analyzed using specific software (Winfood–Medimatica Srl) by a dietitian. The intake of drugs, dietary supplements, pre-, pro-, and synbiotics will be recorded in the same chart. Then, the RT will schedule for each participant follow-up visits every 12 weeks from the enrollment (8–13 GW), then at 14–28 GW and at 29–40 GW. During these visits the CT will perform a full physical examination, anamnestic and clinical data collection, stool sampling (at least 3 g), 7-day food diary collection, Med Diet Score assessment. Each item assigns a score of 0 or 1, with a total score ranging from 0 to 14. The three categories of adherence to MD are divided in ≤5 (low), 6–9 (medium), ≥10 (high) score. Furthermore, to ensure and encourage the completion of the 7-day food diary, one week before each visit, the RT will remind the women by a phone call to fill in the food diary daily for the following week and to return them at the following visit. At delivery a cord blood sample (at least 10 ml) and a breast milk sample (collected within 24 h after delivery) (3 ml) will be collected. All neonatal clinical features will be evaluated by CT. After delivery, for all babies a follow-up visit will be planned every 3 months for the first 12 months of life and then every 6 months until the age of 2 years. At each visit the following procedures will be adopted by CT: full anamnestic and clinical evaluation, body growth assessment, occurrence of allergic disorders, occurrence of other conditions, 7-day food diary, child Mediterranean Diet Quality Index score (KIDMED) evaluation, stool sampling (at least 3 g). At each visit the persistence of breastfeeding will be also assessed and a breast milk sample will be eventually collected (3 ml). In addition, Skin Prick Testing using main pediatric allergens will be performed at 12 and 24 months. All collected data and documents will always remain confidential.

### Evaluation of the occurrence of allergic disorders in the offspring

The occurrence of any allergic disorders in the offspring will be carefully monitored every 6 months for the first 2 years of life by the CT. During these visits, the CT will assess clinical status, body growth, occurrence of allergic symptoms. Unscheduled visits will be performed, if necessary, because of allergic symptoms or other morbidities. Whenever allergic symptoms or other morbidities occurred, parents will be instructed to contact the family pediatrician of the CT to have a medical examination of their child. At each visit, the CT will perform a full physical examination, and then, using standardized criteria, will decide on the atopic manifestation diagnosis (20, 21). The occurrence of atopic manifestation will be investigated, evaluating potential condition in differential diagnosis and the results of allergy screening tests. In case of discordance about an atopic manifestation diagnosis, further evaluation by another pediatric allergist, unaware of the study aims, will be performed. Atopic eczema will be diagnosed by pruritus, typical morphology, and distribution, a chronic or chronically relapsing course, and personal or family atopic history (three of four criteria), in addition to three minor criteria among a list of 21 as reported elsewhere (20). Allergic oculorhinitis will be diagnosed based on the symptoms of rhinitis, such as nasal congestion, sneezing, itching, rhinorrhea, current use of medication for these symptoms and/or conjunctivitis, after exclusion of infection. Allergic urticaria will be diagnosed if at least two episodes of itching eruptions or swelling with typical appearance will be observed by the parents or a physician and will be caused by the same allergen. The diagnosis of asthma in young children with a history of wheezing is more likely if they have: wheezing or coughing that occur with exercise, laughing or crying, or in the absence of an apparent respiratory infection; a history of other allergic disease (eczema or allergic rhinitis), allergen sensitization or asthma in first-degree relatives; clinical improvement during 2–3 months of controller treatment, and worsening after cessation (21). Alternative causes of recurrent wheezing will be considered and excluded. The occurrence of both IgE and non-IgE mediated food allergies will be evaluated using criteria previously adopted by others (22): convincing food allergy, based on the occurrence of suggestive clinical features of food allergy (urticaria, angioedema, atopic dermatitis, asthma, oculorhinitis, diarrhea, regurgitation/vomiting, abdominal pain, constipation, bloody stools, failure to thrive) after the ingestion of a particular food and clear response to the elimination diet; or confirmed food allergy, based on the presence of suggestive clinical features of food allergy, clear response to the elimination diet, positive food allergy screening tests (skin prick tests, serum specific IgE, atopy patch tests), and/or positive oral food challenge (OFC).

### Evaluation of other morbidities during the follow-up period

All babies will be carefully monitored during the study period (through scheduled or unscheduled visits that will be performed by the CT) for the occurrence of infectious diseases and/or chronic non-transmissible conditions (overweight/obesity, autoimmune diseases, malignancies, neuropsychiatric disorders). All diagnoses will be performed according to validated criteria. All data will be collected in a dedicated chart.

### Metagenomic and metabolomic analysis

All fecal and human milk samples will be stored at −80°C and subjected to microbial DNA extraction by RT according to the International Human Microbiome Standard Consortium (IHMSC) Standard Operating Procedures (23).

### Shotgun metagenomics analysis

DNA libraries will be sequenced on Illumina NovaSeq platform, leading to 2 × 150 bp, paired-end reads. Reads filtering will be performed using the Human Sequence Removal pipeline developed within the Human Microbiome Project by using the Best Match Tagger (24). Then, non-human reads will be quality-filtered using PRINSEQ (23): reads with bases having a Phred score <15 will be trimmed and those <75 bp will be discarded. High quality reads will be imported in MetaPhlAn3 (25) to obtain species-level, quantitative taxonomic profiles. Functional profiling will be obtained using HUMAnN3 (26). Genomes of dominant strains will be also reconstructed with a pipeline recently validated (27) and compared, to define if a strain-level variation exists upon intervention.

### Metabolomic analysis

One gram of frozen feces and 1 ml of breast milk will be diluted with saline buffer, vortexed and centrifuged (12,000 × *g*) for 10 min in 2 ml tubes for SCFAs determination. The supernatants will be filtered (0.45 μm) and stored at −20°C until analysis. The extracts will be acidified with 20 μl of 85% (w/v) phosphoric acid and 0.5 ml of ethyl acetate, mixed, centrifuged (12,000 × *g*) for 1 h, and extracted in duplicate. About 0.5 ml of the pooled extract containing the acidified SCFAs will be transferred into a 2 ml glass vial and loaded onto an Agilent Technologies (Santa Clara, CA, USA) 7,890 gas chromatograph (GC) system with automatic loader/injector, combined with Mass Spectrometry (MS). The GC-MS column will be an Agilent 122-7,032 ui (DB-WAX-U, Agilent Technologies, Santa Clara, CA, USA) of 30 m, internal diameter of 0.25 mm, and film thickness of 0.25 μm. The GC-MS will be programmed to achieve the following run parameters: initial temperature of 50°C, hold of 1 min, ramp of 10°C min^–1^ up to a final temperature of 180°C, total run time of 20 min, gas flow of 70 ml min^–1^ splitless to maintain 12.67 p.s.i. column head pressure, and septum purge of 2.0 ml min^–1^. Helium will be the carrier gas (1.5 ml min^–1^ constant). Parameters of mass spectrometer will be source at 230°C and MS Quad at 150°C. The GraphPad PRISM eight program will be used to determine the concentration in mm. The data will be inserted in the “XY” form in which in the “X” frame the values of the straight concentration-response were reported, while in the “Y” box the values of the area under the curve (AUC) related to the peaks obtained from the mass gas will be reported. The AUC values of the single samples (obtained from the mass gas) will be interpolated with the line X (concentration-response) to determine the corresponding mm.

